## Abstract

**Background:**

Blood pressure (BP) control and reduction of urinary protein excretion using agents that block the renin–angiotensin aldosterone system are the mainstay of therapy for chronic kidney disease (CKD). Research has confirmed the benefits in mild CKD, but data on angiotensin-converting enzyme inhibitor (ACEi) or angiotensin receptor blocker (ARB) use in advanced CKD are lacking. In the STOP-ACEi trial, we aim to confirm preliminary findings which suggest that withdrawal of ACEi/ARB treatment can stabilize or even improve renal function in patients with advanced progressive CKD.

**Methods:**

The STOP-ACEi trial (trial registration: current controlled trials, ISRCTN62869767) is an investigator-led multicentre open-label, randomized controlled clinical trial of 410 participants with advanced (Stage 4 or 5) progressive CKD receiving ACEi, ARBs or both. Patients will be randomized in a 1:1 ratio to either discontinue ACEi, ARB or combination of both (experimental arm) or continue ACEi, ARB or combination of both (control arm). Patients will be followed up at 3 monthly intervals for 3 years. The primary outcome measure is eGFR at 3 years. Secondary outcome measures include the number of renal events, participant quality of life and physical functioning, hospitalization rates, BP and laboratory measures, including serum cystatin-C. Safety will be assessed to ensure that withdrawal of these treatments does not cause excess harm or increase mortality or cardiovascular events such as heart failure, myocardial infarction or stroke.

**Results:**

The rationale and trial design are presented here. The results of this trial will show whether discontinuation of ACEi/ARBs can improve or stabilize renal function in patients with advanced progressive CKD. It will show whether this simple intervention can improve laboratory and clinical outcomes, including progression to end-stage renal disease, without causing an increase in cardiovascular events.

## INTRODUCTION

Chronic kidney disease (CKD), Stages 3–5, affects 1 in 10 adults in the UK and reflects progressive scarring of the kidneys regardless of the original disease and is associated with a high prevalence of cardiovascular disease [1]. Advanced CKD (Stage 4 or 5) is associated with a significantly increased risk of death [hazard ratio (HR): 3.6; 95% confidence interval (CI) 3.2–4.0] [2] and a 50-fold increased requirement for dialysis, in comparison with age-matched individuals with presumed normal kidney function [3–6]. Advanced CKD has a major negative impact on a range of other clinical outcomes including quality of life [7, 8] and carries a high economic burden either through associated cardiovascular or metabolic bone disease or due to the high cost of renal dialysis (∼£30 000/year).

Irrespective of the underlying cause of CKD, attention has focused primarily on blood pressure (BP) control and reduction of urinary protein excretion using agents that block the renin–angiotensin aldosterone system and reduce intra-glomerular pressure over and above their effect on BP. Studies by Lewis *et al*. [9, 10] and Brenner *et al*. [11] have shown that angiotensin-converting enzyme inhibitor (ACEi) and angiotensin receptor blockers (ARBs) reduce the progression of renal disease [12–16]. Data from the HOPE, LIFE and ALLHAT studies have confirmed the benefit of ACEi use in mild CKD [estimated glomerular filtration rate (eGFR) >60 mL/min/1.73m^2^ with proteinuria or structural defects] [17–20].

Few studies have included patients with advanced CKD at baseline. Moreover, it is difficult to dissociate the beneficial effect of ACEi from BP control. Indeed, in the HOPE sub-study using 24-h ambulatory BP in place of office BP, there was a significant reduction in BP from baseline in patients assigned to ramipril, which may have been an important mediator of benefit [18]. Ruggenenti *et al.* in a *post hoc* analysis of 322 patients suggested that therapy should be offered to all patients with CKD, even those with a GFR between 10 and 30 mL/min/1.73 m^2^ [21]. In this seminal study, there was no ‘nephroprotective’ effect when baseline proteinuria was <1.5 g/24 h, suggesting that the beneficial effects of ACEi may be limited to those with ‘pure’ glomerular disease rather than those with low-level proteinuria who may have ischaemic CKD. A Cochrane review of 49 studies containing 12 067 diabetic patients at all stages of CKD found that ACEi and ARBs improved hard end point [end-stage renal disease (ESRD)] and other outcomes, and appeared to reduce mortality (relative risk 0.78; 95% CI 0.61–0.98) [22]. The authors, however, cautioned against the conclusion that ACEi prevents progression of CKD, suggesting that any initial benefit may be due to their anti-proteinuric effects (probably reflecting better overall BP control), that there was little robust evidence of benefit in advanced CKD and that conclusions were based mainly on composite end points [22].

The rigor of some of these studies, which failed to dissociate renoprotective from antihypertensive effects of ACEi/ARBs [18], is now being questioned. Renoprotection from ACEi/ARB may be lost in more advanced disease where significant ischaemic nephropathy is present. This hypothesis is supported by reports in diabetic and non-diabetic patients with CKD indicating that ACEi/ARBs may accelerate renal progression, in spite of a beneficial anti-proteinuric effect [23–25]. Combined ACEi/ARB treatment has been shown to worsen renal outcomes in patients at high cardiovascular risk and increases the risk of hyperkalaemia and acute kidney injury [26–28]. The Telmisartan Randomized Assessment Study in ACE intolerant subjects with cardiovascular disease (TRANSCEND) demonstrated both a greater decline in eGFR and greater incidence of doubling of serum creatinine on Telmisartan (HR 1.59; 95% CI 1.04–2.41) [29].

In a recent observational study, withdrawal of ACEi/ARB therapy in 52 older patients with advanced CKD led to a mean increase in eGFR of 10 mL/min/1.73 m^2^ over 12 months and an increase or stabilization in eGFR in all but four patients. There was a small increase in BP but no change in risk of cardiovascular events [30]. There was also an association between the increase in BP levels upon discontinuation of ACEi/ARB and improved renal function [31]. The close interaction of the kidney and the heart is critical to survival, and the risk factors for poor cardiovascular outcomes in the general population and in early CKD are associated with better outcomes in advanced CKD [32, 33]. There are no studies assessing the benefits of ACEi/ARB therapy in cardiovascular risk reduction in advanced non-dialysis CKD. Indeed, although lowering BP reduces cardiovascular events, evidence suggests that ACEi/ARBs are not superior to other antihypertensives in this regard [34, 35]. Several randomized controlled studies in dialysis patients have shown increased cardiovascular events with the use of ACEi [36–38]. Indeed, the rate of decline of renal function remains a strong predictor of mortality [39–41].

## RESEARCH QUESTION

Does a strategy of discontinuing ACEi, ARBs or their combination in patients with advanced (Stage 4 or 5) progressive CKD lead to stabilization or improvement in renal function over a 3-year follow-up period, provided that good BP control is maintained with other agents, compared with a strategy of continuing ACEi and/or ARB?

## MATERIALS AND METHODS

### Study design

STOP-ACEi (trial registration: current controlled trials, ISRCTN62869767) is an investigator-led, multicentre, open-label, randomized controlled clinical trial of 410 participants aged 18 years or over with advanced (Stage 4 or 5) progressive CKD receiving ACEi, ARBs or both. Patients will be followed up 3 monthly for 3 years (Figure 1).

**FIGURE 1: GFV346F1:**
[figure not shown]
Schema for STOP-ACEi trial. BCP, biochemical profile (including urea and electrolytes and liver function tests); BMI, body mass index; FBC, full blood count; QOL, quality of life.

### Recruitment

Participants will be recruited from at least 15 UK renal units. Site staff will screen for potential eligible participants using the inclusion/exclusion criteria. If the participant is interested in taking part, the trial will be discussed with them in detail, and they will have the opportunity to ask questions. Participant eligibility will be confirmed with regard to the inclusion and exclusion criteria, and informed consent will be sought.

### Inclusion and exclusion criteria

Inclusion criteria are as follows:Aged ≥18 years (male or female)CKD Stage 4 or 5 [eGFR <30 mL/min/1.73 m^2^ using the modification of diet in renal disease (MDRD) equation] and must not have received a kidney transplant or be on dialysisProgressive deterioration in renal function (fall in an eGFR of >2 mL/min/year over previous 24 months) as measured by linear regression analysis based on a minimum of three eGFR measurements, with at least one reading from the previous 3 monthsTreatment with either an ACEi or ARB or a combination of both for >6 months with at least 25% of the maximum recommended daily doseResting BP ≤160/90 mmHg when measured in accordance with British Hypertension Society guidelines in clinic or recent home BP reading within the previous month or a 24-h ambulatory BP measurement within the last 3 monthsAt least 3 months of specialist renal follow-upWritten, signed informed consent to the trial

Exclusion criteria are as follows:Aged <18 yearsUncontrolled hypertension (>160/90 mmHg) or requirement for five or more agents to control BPUndergoing dialysis therapyPrevious kidney transplantAny condition that, in the opinion of the investigator, makes the participant unsuitable for trial entry due to prognosis/terminal illness with a projected survival of <12 monthsHistory of myocardial infarction or stroke in preceding 3 monthsParticipation in an interventional research study in preceding 6 weeksPregnancy confirmed by positive pregnancy test or breastfeedingInability to provide informed consent (e.g. due to cognitive impairment)Immune-mediated renal disease requiring disease-specific treatmentKnown drug or alcohol abuseInability to comply with the trial schedule and follow-up

### Study enrolment and randomization

Following informed consent and completion of the baseline assessments, participants will be randomized into the trial in a 1∶1 ratio to either continue with their ACEi and/or ARB treatment (control arm) or to discontinue their ACEi and/or ARB treatment (experimental arm). Randomization will be provided by a computer-generated programme at the Clinical Trials Unit, using a minimization algorithm to ensure balance between the arms with regard to important clinical variables. The minimization variables will be diabetes (Type I diabetes, Type II diabetes or non-diabetic), BP {mean arterial pressure [MAP] measured as [(2 × diastolic) + systolic]/3; <100 or ≥100}, age (<65 or ≥ 65 years), proteinuria (protein:creatinine ratio (PCR) <100 or ≥100) and eGFR (<15 or ≥ 15 mL/min).

### Study treatment

#### Active treatment (experimental)

All ACEi and/or ARB treatment will be discontinued. In order to compensate for the loss of antihypertensive activity, additional antihypertensive treatment will be commenced to keep BP within recommended guidelines. Any antihypertensive agents used in routine clinical practice are permitted to control BP throughout the trial, but excluding ACEi or ARBs. The choice of antihypertensive will depend on other treatment being taken by the participant and will be at the discretion of the responsible clinician. Any antihypertensive agent used in routine clinical practice is permitted, but excluding ACEi and ARBs except as a last resort.

#### Control arm

Participants will continue on ‘standard’ care and will continue with their ACEi and/or ARB treatment. The choice and dose of ACEi and/or ARB will be at the discretion of the responsible clinician.

#### Both treatment groups

In both groups, BP will be controlled to the target pressure outlined in the National Institute for Health and Care Excellence (NICE) Hypertension guideline and NICE CKD guideline [42, 43] of ≤140/85 mmHg. The monitoring of BP will be as per the NICE CKD guideline.

#### Blinding

Trial treatment will be open label, due to the practical difficulties and costs associated with using placebo in a trial of drug withdrawal. However, the primary outcome measure is an objective laboratory measure that reduces the need for blinding. Additionally, investigators taking part in the trial will remain blind to all trial outcome data for the duration of the trial to minimize bias, with un-blinded data presented only to the independent Data Monitoring and Ethical Committee (DMEC).

### Assessments

Patients will be assessed at 3 monthly intervals from baseline to 3 years in the patient’s routine outpatient clinic visit as per the trial schedule of assessments (Table 1) [42].

**Table 1. GFV346TB1:** Schedule of assessments

Trial visit number	1	Phone call	2	3	4	5	6	7	8	9	10	11	12	13
Month	0		3	6	9	12	15	18	21	24	27	30	33	36
Check eligibility against inclusion/exclusion criteria, informed consent, randomization	✓													
Demographic and lifestyle data^a^	✓													
Medical history including cardiovascular comorbidities and CKD aetiology	✓													
Height	✓													
Weight and BMI	✓					✓				✓				✓
BP	✓		✓	✓	✓	✓	✓	✓	✓	✓	✓	✓	✓	✓
6 min walk test	✓					✓				✓				✓
KDQoL-SF™ v1.3 questionnaire	✓					✓				✓				✓
12-lead ECG	✓					✓				✓				✓
Record data from existing cardiac echocardiograms	✓		✓	✓	✓	✓	✓	✓	✓	✓	✓	✓	✓	✓
Record medication changes including ESA dose	✓	✓	✓	✓	✓	✓	✓	✓	✓	✓	✓	✓	✓	✓
Assess compliance with trial treatment allocation		✓	✓	✓	✓	✓	✓	✓	✓	✓	✓	✓	✓	✓
Adverse event documentation		✓	✓	✓	✓	✓	✓	✓	✓	✓	✓	✓	✓	✓
Lab assessments	✓		✓	✓	✓	✓	✓	✓	✓	✓	✓	✓	✓	✓
Routine tests (performed locally)^b^	✓					✓				✓				✓
C-Reactive Protein (performed locally)	✓					✓				✓				✓
Additional trial tests (analysed centrally)^c^	✓					✓								✓
Serum and urine samples taken for optional biomarker analysis														

^a^To include date of birth, gender, ethnicity, smoking status and alcohol intake.

^b^To include creatinine, eGFR, haemoglobin, mean cell volume, mean corpuscular haemoglobin, platelets, sodium, potassium, bicarbonate, calcium, phosphate, alkaline phosphatase, albumin, total protein, alanine transferase and urinary protein:creatinine or albumin:creatinine ratio.

^c^To include cystatin-C, NT-proBNP and ACE/renin levels in a sample of participants.

Demographic data (e.g. date of birth, gender, smoking status, weight, height) and a detailed disease history (e.g. cardiovascular comorbidity, antihypertensive medications) will be collected at baseline. BP will be recorded at each visit, and changes to antihypertensive and other concomitant medications will be recorded. A 12-lead electrocardiogram (ECG), quality of life (using KDQOL-SF^TM^ v1.3) and physical function (using 6 min walk test) will be collected at baseline and then annually.

For the purpose of the trial, urine and blood samples will be taken at baseline and each 3 monthly assessment. These samples will be used for routine tests and additional tests as part of the trial (Table 1).

### Primary outcome measure

The primary outcome measure is difference in renal function measured using the MDRD four-variable eGFR at the 3 years of follow-up.

### Secondary outcome measures

#### Renal events

The number of participants starting renal replacement therapy or sustaining a >50% decline in eGFRTime taken to reach ESRD or need for renal replacement therapy

#### Quality of life and physical function

Participant quality of life and well-being (KDQOL-SF™ v1.3 questionnaire)Participant physical function (6 min walk test)

#### Clinical events

Hospitalization rates from any causeBP

#### Laboratory measures

Serum cystatin-C

#### Safety

Safety of intervention related to potential harm (e.g. increased cardiovascular events such as heart failure, myocardial infarction, stroke or death, participant survival in each group)

### Mechanistic outcome measures

Urine protein excretionBlood haemoglobin concentrationDose of erythropoietin stimulating agent (ESA) administered

### Statistical considerations

#### Sample size

An observational study provided data on eGFR in 52 patients with advanced CKD in the 12 months prior to stopping ACEi/ARB treatment, at the point of stopping ACEi/ARB and 12 months after stopping (Table 2) [31]. These data form the basis of the sample size calculation.

**Table 2. GFV346TB2:** Data that formed the basis of the sample size calculation

Time point relative to stopping ACEi/ARB	eGFR (mL/min/1.73 m^2^), mean ± SE (SD)
−12 months	22.9 ± 1.4 (10.1)
0	16.38 ± 1 (7.2)
+12 months	26.6 ± 2.2 (15.9)

eGFR in patients with CKD who underwent ACEi/ARB withdrawal in a previously published study.

To err on the side of caution, the largest standard deviation was used to estimate the variability in eGFR (i.e. SD of 16 mL/min/1.73 m^2^) for the sample size calculation. To detect a minimum relevant difference between groups of 5 mL/min/1.73 m^2^ (i.e. effect size of 0.31) with 80% power and alpha = 0.05 (using a two-sample *t*-test), a total of 410 participants (205 per group) will need to be recruited (this includes allowance for 20% dropout). Data from Beddhu *et al*. who used propensity scores in a multivariate model in Dialysis Morbidity and Mortality Study Wave 2 patients showed that each 5-mL/min fall in MDRD GFR was associated with an increased hazard of death in a multivariable Cox model (HR 1.14; P = 0.002) [44].

#### Statistical analysis

The Statistical Analysis Plan will describe the planned analyses for STOP-ACEi in full detail. A summary of the main analyses are given here. All analysis will be based on the intention to treat principle, and a P-value of <0.05 will be considered statistically significant. The primary outcome is the continuous measure eGFR at 3 years. These data will be summarized using means and standard deviations, with differences in means and 95% CIs reported. The two groups will be compared at 3 years using both a two-sample *t*-test and ANCOVA to adjust for baseline values. Longitudinal plots of the data over time will be constructed for visual presentation of the data. As a secondary analysis, a repeated measures analysis, including a treatment by time cross-term, will be carried out on all data across the 3 years of follow-up.

Continuous secondary outcome measures (e.g. BP, quality of life) will be analysed in the same way as the primary outcome. Categorical (dichotomous) outcome measures (e.g. hospitalization rates) will compare the proportion of participants and percentages using a χ^2^ test, with relative risks and 95% CIs reported. Time-to-event outcomes (e.g. time to ESRD, mortality) will be analysed using survival analysis and log-rank methods. Kaplan–Meier survival curves will be constructed for visual presentation of time-to-event comparisons. Treatment effects will be expressed as HRs with 95% CIs.

Several *a priori* subgroup analyses with respect to the minimization variables for both primary and secondary outcomes will be performed. These analyses will be considered hypothesis generating.

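### The primary outcome has two unranked tests, a t-test and a baseline-adjusted ANCOVA; one adjusted analysis should be named as decisive

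*Protocol article*

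**What the plan says.** The Statistical analysis section of the protocol article defines the endpoint: "The primary outcome is the continuous measure eGFR at 3 years". It sets a single threshold for all analyses: "a P-value of <0.05 will be considered statistically significant". It then gives the comparison: "The two groups will be compared at 3 years using both a two-sample" t-test together with "ANCOVA to adjust for baseline values".

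Neither test is ranked above the other. The same section does rank other analyses. The longitudinal model is introduced with "As a secondary analysis, a repeated measures analysis, including a treatment by time cross-term", and subgroup analyses are described as exploratory. Continuous secondary outcomes, such as blood pressure and quality of life, are to be handled by the same methods as the primary outcome.

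Under Study enrolment and randomization, allocation is by minimisation: "The minimization variables will be diabetes (Type I diabetes, Type II diabetes or non-diabetic"), followed by mean arterial pressure, age, protein:creatinine ratio and eGFR split at 15 mL/min. The Statistical analysis section mentions these variables only as subgroup factors.

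The Sample size section uses a two-sample t-test "with 80% power and alpha = 0.05", but does not say that the t-test decides the trial.

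**The concern.** Two tests of one endpoint share one threshold, and no rule says which of them answers the trial's question. They are correlated but can fall on opposite sides of 0.05. The trial would then have one significant and one non-significant result with equal claim to be primary, and the choice could be made after seeing the data.

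The tests are also not equally suited to the design. The t-test ignores baseline eGFR, which is expected to predict later eGFR. Minimisation removes chance imbalance in eGFR category and four other factors, but the t-test's standard error still allows for that imbalance. If those factors predict outcome, the standard error is too large. Interval width, power and the actual type I error therefore all depend on which test is taken as decisive.

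**Working it through.** **Inputs.** From the Sample size section: SD 16, difference 5 (effect size 0.31), 80% power, alpha 0.05, 410 participants (205 per arm) including 20% dropout. The article does not give the correlation ρ between baseline and 3-year eGFR, so a range of 0.3 to 0.9 is assumed.

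**The plan's own figure.** n per arm = 2(1.96 + 0.842)²/0.31² = 163.4, rounded up to 164. Then 164/0.8 = 205 per arm, total 410. The stated figure is reproduced with a two-sided test. With the unrounded 5/16, n is 161, then 202 after dropout, total 404. A one-sided test gives 127, or 159 after dropout, and does not reproduce it.

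**Precision and power, 164 completers per arm.** ANCOVA residual SD = 16√(1−ρ²). SE = SD × √(2/164). Power = Φ(5/SE − 1.96). The 95% half-width is 1.96 × SE. For the t-test, SE = 16 × 0.1104 = 1.767 and power = Φ(2.830 − 1.96) = 0.808.

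**Error rates under simple randomisation.** Under the null the two statistics are approximately bivariate normal with correlation √(1−ρ²). P(either) is the probability that at least one exceeds 1.96 in absolute value. P(both) = 0.05 + 0.05 − P(either). P(disagree) = P(either) − P(both).

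| ρ | Residual SD | Power | CI half-width | Either | Both | Disagree |
|---|---|---|---|---|---|---|
| t-test | 16.0 | 80.8% | 3.46 | | | |
| 0.3 | 15.3 | 84.3% | 3.30 | 6.4% | 3.6% | 2.8% |
| 0.5 | 13.9 | 90.4% | 3.00 | 7.3% | 2.7% | 4.7% |
| 0.7 | 11.4 | 97.7% | 2.47 | 8.3% | 1.7% | 6.6% |
| 0.9 | 7.0 | >99% | 1.51 | 9.2% | 0.8% | 8.5% |

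**Error rates under minimisation.** The trial does not use simple randomisation, so 4,000 null trials of 328 completers were simulated for each scenario. Assumptions: allocation to the favoured arm with probability 0.8; five binary factors, one being eGFR split at 15 and the other four at 50% prevalence; baseline eGFR with mean 16.4 and SD 7.2, from Table 2 at the time of stopping. The other four factors explain either none or 10% of outcome variance. Simulation error is about 0.3 percentage points on each rate.

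| ρ | Variance from other four | t-test | ANCOVA, baseline only | Either | Both | ANCOVA, all factors |
|---|---|---|---|---|---|---|
| 0.5 | 0 | 3.6% | 5.1% | 6.0% | 2.7% | 5.1% |
| 0.7 | 0 | 1.7% | 4.5% | 4.9% | 1.3% | 4.5% |
| 0.5 | 10% | 2.5% | 3.8% | 4.4% | 1.9% | 5.0% |
| 0.7 | 10% | 1.0% | 2.7% | 3.0% | 0.7% | 4.9% |

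A separate simulation, also with assumed inputs, gave about 4 to 7% for either test, 1.7 to 4.3% for the t-test, and 3 to 3.5% for baseline-only ANCOVA when the other factors explained 10% of variance. Together the either-test range is about 3 to 7%.

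**Simulated power and disagreement at a true difference of 5** (2,000 minimised trials each):
- ρ 0.5, no variance from the other four: t-test 0.831, baseline-only ANCOVA 0.907; disagreement 0.911 − 0.826 = 0.085.
- ρ 0.5, 10%: 0.846 and 0.923, or 0.941 with all factors; disagreement 0.927 − 0.842 = 0.085.
- ρ 0.7, 10%: 0.871 and 0.987, or 0.993 with all factors; disagreement 0.987 − 0.871 = 0.116.

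**The case against.** The strongest reply is that the article is only a summary: "The Statistical Analysis Plan will describe the planned analyses for STOP-ACEi in full detail". The plan may name the deciding test and list the covariates. This stands for the covariate list. The article neither includes nor excludes diabetes, mean arterial pressure, age and proteinuria as covariates, and ANCOVA on baseline eGFR already covers one of the five factors. A reader might infer that the trial will not adjust for its minimisation variables, but silence in a summary does not show that. The reply does not dispose of the main point, because the article itself commits to two tests and ranks neither while ranking other analyses.

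A reader might also infer that the type I error is inflated. That requires a rule that either test suffices, and the article states none. If both tests must be significant, the error is below 5%. The 6 to 9% figure also assumes simple randomisation, which this trial does not use.

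Finally, a reader might conclude that precision is lost outright. Baseline-adjusted ANCOVA is already planned, so its gain is available if it decides. If the t-test decides, the trial still has the roughly 80% power it was sized for. Adding the other four factors raised simulated power only from 0.923 to 0.941 (ρ 0.5) and from 0.987 to 0.993 (ρ 0.7).

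**Conclusion.** The article leaves the primary result undefined when the t-test and ANCOVA disagree. Under the simulated design, with a true difference of 5, they disagreed in about 8.5 to 11.6% of trials. Choosing the t-test would give up roughly 9 to 17 percentage points of power by the formula (81% against 90% or 98%) at an assumed ρ of 0.5 or 0.7. It would also mean using a test that is conservative to the extent that the minimisation factors are prognostic.

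No direction for the overall error rate is established, because it depends on an unstated rule and on the allocation method. The main benefit of adding the other minimisation variables is a correctly calibrated standard error; the further power gain is likely modest. The sample size is not in error.

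The missing ranking can be read directly from the text. The sizes rest on assumed values of ρ, the minimisation probability, the factor prevalences and the variance explained.

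**What to change.** Name one primary analysis: ANCOVA of 3-year eGFR adjusted for continuous baseline eGFR and the other minimisation variables (diabetes type, mean arterial pressure, age and protein:creatinine ratio). State that its P-value and confidence interval give the primary result. Label the unadjusted t-test supportive or descriptive. Apply the same ranking to the continuous secondary outcomes that follow the primary method, each adjusted for its own baseline value and the minimisation variables.

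If the statistical analysis plan already says this, a cross-reference is enough. Otherwise the cost is a sentence or two, settled before any unblinded comparison. The covariates are already recorded at randomisation, and neither sample size nor data collection changes.

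### The primary ANCOVA for 3-year eGFR names baseline values but not the eligibility eGFR slope; adding the slope is a cheap, optional gain in precision, not the repair of an error

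*Protocol article*

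**What the plan says.** Under Statistical analysis, the protocol article states "The primary outcome is the continuous measure eGFR at 3 years". The arms are compared at 3 years by a two-sample t-test and by "ANCOVA to adjust for baseline values", with a repeated measures model containing a treatment-by-time term as a secondary analysis. The section is introduced with "The Statistical Analysis Plan will describe the planned analyses for STOP-ACEi in full detail. A summary of the main analyses are given here".

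Under Inclusion and exclusion criteria, each participant must show a "fall in an eGFR of >2 mL/min/year over previous 24 months". The method is fixed too: this decline is to be taken "as measured by linear regression analysis based on a minimum of three eGFR measurements", and one or more of those values must date from the last 3 months.

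Under Study enrolment and randomization, the minimisation variables are diabetes, mean arterial pressure, age, proteinuria and eGFR. The rate of decline is not among them.

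Under Sample size, the trial is sized on an unadjusted t-test with "SD of 16 mL/min/1.73 m"² and an "effect size of 0.31".

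**The concern.** The population is selected for falling eGFR, and the outcome is eGFR three years on. Where a participant ends depends on the starting level and on how fast the level is falling. A model with baseline eGFR alone gives the same expected 3-year value to two participants who start level but were declining at very different rates. The rate is known before randomisation, and sites must derive it to confirm eligibility. If it predicts the outcome beyond baseline, leaving it out makes the confidence interval for the treatment difference wider than it need be. Precision is all that is at stake. Validity is not in question.

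**Working it through.** **1. The plan's own figure.** Inputs from Sample size: difference 5, SD 16, 80% power, alpha 0.05 (two-sided assumed), 1:1 allocation, 20% dropout.
- n per arm = 2(1.96 + 0.8416)² / d².
- With d rounded to 0.31: 2 × 7.849 / 0.0961 = 163.4, so 164 per arm and 328 in total; 328 / 0.8 = 410. This matches the protocol.
- With d = 5/16 = 0.3125: 161 per arm, 322 in total, 403 after dropout, which is within 3%.
- At 164 evaluable per arm, the unadjusted comparison with SD 16 has about 81% power.

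No covariate enters this calculation, so leaving out the slope takes nothing from the stated power.

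**2. What a covariate can add.** Let rho be the correlation of baseline with 3-year eGFR, and r the partial correlation of slope with 3-year eGFR given baseline. Then residual SD = 16 × √(1 − rho²) × √(1 − r²), and the standard error falls by 1 − √(1 − r²). The documents give neither rho nor r, so both are assumed.

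| r | Fall in SE | Power, rho = 0.5 |
|---|---|---|
| 0 (baseline only) | 0% | 90.4% |
| 0.1 | 0.5% | 90.7% |
| 0.2 | 2.0% | 91.5% |
| 0.3 | 4.6% | 92.9% |
| 0.4 | 8.3% | 94.6% |
| 0.5 | 13.4% | 96.5% |

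With rho = 0.7, power starts at 97.7% and reaches 98.6% at r = 0.3.

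**3. What r might plausibly be.** A simulation used these assumed inputs: eGFR 18 (SD 6); slope mean −2.5 and SD 2 or 3 mL/min/year before selection; within-person CV 7.5%; 3 to 6 readings over 24 months; entry only if the observed slope was below −2 and baseline eGFR below 30. Three-year eGFR was regressed on baseline, then on baseline plus slope. Without a floor, 12-25% of simulated 3-year values were at or below zero, so a floor of 5 mL/min was also applied.

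| Assumed pre/post slope correlation | Fall in residual variance, floor 5 | No floor |
|---|---|---|
| 0.2 | 0.2-1.0% | 0.4-1.4% |
| 0.4 | 1.8-3.7% | 2.7-5.6% |
| 0.6 | 4.7-8.3% | 8.2-14.6% |

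**4. In trial terms.** Equivalent extra evaluable participants = 328 × (1/(1 − v) − 1), where v is the fall in variance; the interval narrows by 1 − √(1 − v).
- v = 0.01: 3 participants, interval 0.5% narrower.
- v = 0.037: 13 participants, 1.9% narrower.
- v = 0.083: 30 participants, 4.2% narrower.

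The last case corresponds to r = √0.083 = 0.29. In the table under step 2 that is a rise from 90.4% to about 93% power.

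**5. What could shrink it.**
- *Noisy slopes.* Three readings at −2, −1 and 0 years have a sum of squares of 2, so slope reliability = s² / (s² + e²/2), with true slope SD s and within-person SD e. For s and e each between 1.5 and 3 (assumed), this runs from 2.25/(2.25 + 4.5) = 0.33 to 9/(9 + 1.125) = 0.89.
- *Larger outcome SD.* The unfloored simulated outcome SD is about 8-10.6, against 16 in the protocol. If the remaining variance is unrelated to slope, the gain falls to 0.1-4.1%.

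**The case against.** The strongest answer is that nothing here is wrong. The article calls its analysis text a summary and defers full detail to the SAP, which is not at hand. A reader might infer that the plan adjusts for baseline eGFR alone and rules out the slope. The text does not close the covariate list, so that inference is not supported. What stands is narrower: the article names an adjustment for its primary comparison, and the slope is not in it.

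A reader might also infer that the omission biases the result or leaves the trial underpowered. Neither follows. Randomisation protects the comparison, type I error is unaffected, and step 1 shows that the stated power relies on no covariate. Chance imbalance in rate of decline is already allowed for in the standard error, as for any unadjusted covariate. Selection on an observed fall may make the baseline reading low by chance, but it does so in both arms alike.

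It is also tempting to quote the unfloored upper end, 14.6% of variance or 328 × (1/0.854 − 1) = 56 participants, as what is being lost. That figure needs a slope correlation of 0.6 and allows impossible negative eGFR values. A participant at 18 losing 8 mL/min/year, for instance, would reach 18 − 24 = −6.

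Finally, the trial's own premise cuts against a large gain. In Table 2, mean eGFR falls from 22.9 to 16.38 before withdrawal and then rises to 26.6, with the SD growing from 7.2 to 15.9. If withdrawal alters trajectories in this way, the earlier slope may predict little in the experimental arm. This objection stands, and it limits the size of the benefit.

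**Conclusion.** The point holds as a low-severity efficiency suggestion. The baseline-adjusted ANCOVA is a sound primary analysis. Adding the eligibility slope improved precision in every simulated scenario, but modestly: with the floor, residual variance falls by under 1% to about 8% as the assumed pre/post slope correlation goes from 0.2 to 0.6. These sizes depend on assumed slope variation, measurement error, number of readings and floor, none of which the documents supply. The true gain could be negligible. The case for acting is the low cost, not the size of the benefit.

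**What to change.** In the Statistical analysis section, and in the SAP if it does not already say so, pre-specify the eligibility regression slope as a continuous covariate alongside baseline eGFR in the ANCOVA, and carry it into the repeated measures analysis. Adding the mean of the earlier readings is optional; it overlaps with the other two covariates and brings little more.

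Record the slope, or the dated readings behind it, on the baseline form. Include participants already randomised (118 of 410 on 11 September 2015, per Trial status). Table 1 of the article does not list these readings separately, so check whether they are already captured.

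The cost is a line of analysis wording and transcription of laboratory values that sites have already used to confirm eligibility. No new tests, visits or participants are needed, and the sample size need not change. The covariate should be fixed before any comparison by arm is seen.
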